Of the measurable lesions observed at the registration of this study (baseline), the top 5 largest lesions in diameter (the long diameter for non-lymph node lesions and the short diameter for lymph node lesions) will be selected as target lesions, with at most 2 lesions selected from each organ. The lesions will be selected with the consideration that the selected lesions should be present in organs with measurable lesions spread evenly as much as possible and should show good reproducibility of measurement on repeated examination (i.e., ease of measurement). The site, testing method, date of test, long diameter of non-lymph node lesions, short diameter of lymph node lesions, and sum of the long and short diameters of the selected target lesions will be recorded in the order of cranial to caudal localization.

(3) Selection of non-target lesions and baseline evaluation

For all lesions that are not selected as target lesions, the site, testing method, and date of test will be recorded as "non-target lesions" regardless of whether the lesions are measurable or not. When a number of similar lesions are observed in the same region of the same organ, such lesions may be recorded as a single non-target lesion.

(Examples: multiple pelvic lymphadenopathy and multiple hepatic metastasis.)

(4) Determination of tumor reduction effect

Therapeutic response evaluation will be conducted at the discretions of primary physicians because this study is observational in nature. However, exacerbation of the condition may be observed in the early period after the initiation of the treatment because the study is on breast cancer with low sensitivity to endocrine therapy. Response evaluations will be conducted at about 3 and 6 months to ensure the safety of research subjects and avoid missing the optimum timing for determining treatment policy.

Evaluation of target and non-target lesions will be conducted using the same test methods as those used before registration, including the same photographing conditions such as contrast agent and slice thickness to measure the major axis of the target lesion (the short diameter for lymph node) and to record the disappearance of non-target lesions, the presence or absence of progression, and the presence or absence of new lesions.

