| Unequivocal PD                 | Yes or No                | PD               |
| Any                            | Yes                      | PD               |

(6) Best overall response

The best overall response will be considered in the order of CR > PR > SD > PD > NE. The overall evaluation at the best time point from the initiation of treatment through to the initiation of post-treatment will be considered to be the best overall response.

Meanwhile, determination of CR or PR in 4-week periods is not necessary in this study. When an overall response corresponds to the definition given for multiple categories, it will be categorized into the best-fitted category in the order of CR > PR > SD > PD > NE.

SD determination shall satisfy the SD standards after 6 weeks from the start of treatment. When an obvious deleterious change (exacerbation) of the disease is observed before the first effect determination, it will be considered to be PD when no imaging determination is implemented and NE when the determination was not conducted because of discontinuation of treatment due to adverse events or rejection by a subject.

(7) Clinical progression

Progression will be determined in accordance with the following criteria when using a method other than those defined in {3.8 (4) Determination of tumor reduction effect} or when progression in unmeasurable lesions is determined. However, progression will not immediately be determined even when a case corresponds to the following criteria but the judgment of a clinical investigator is prioritized. When image assessment is available, the image assessment will be prioritized.

- ① Confirmation of progression by ultrasound: When obvious progression such as emergence of new lesions, increased pleural effusion, etc. is observed by ultrasound.
- ② Confirmation of progression in bone lesion: When increased accumulation of bone is observed by scintigram or PET, or emergence of new lesions is observed in a bone lesion.
- ③ Exacerbation of subjective symptoms: When a clinical investigator determines there to have been progression, such as obvious exacerbation of bone pain in bone metastasis, obvious exacerbation of a sensation of dyspnea in lung metastasis, etc.

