The response rate is the rate of patients whose best overall response {3.8(6) Best overall response} in a target population with measurable lesions is CR or PR as a proportion of all the cases that underwent treatment.

(7) Health-related quality of life (HRQoL)

See "5.5 Survey of health-related quality of life".

(8) Adverse events (toxicity)

Adverse events that are observed from registration to the discontinuation of the protocol treatment will be evaluated in all treated cases (see "19 Evaluation and reporting of adverse events").

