#### (2) Intervention

Intervention is defined as "A practice for investigational purpose to control the presence or absence of factors that can affect a variety of events related to human health (including activities to maintain and promote good health and medical practices such as medication and examinations for prevention, diagnosis, and treatment of the patients), or the degree of such factors. The above-defined intervention also includes medical techniques beyond usual medical practice that are conducted for investigational purposes." in Chapter 1, Part 2 "Glossary" (3) of the guidelines.

The treatment implemented in this study will be conducted as regular clinical practice based on

the preferences of medical staff and patients using drugs covered by insurance. Therefore, this study does not correspond to the treatment defined in the "Objectives of the study". A total of 3 imaging evaluations conducted at the time of registration and at 3 and 6 months are specified as investigations in this study. However, these evaluations do not correspond to medical practice exceeding the range of regular medical examination as an evaluation approach of drug therapy for metastatic breast cancer. In addition, evaluation of QoL does not correspond to medical practice. As mentioned above, this study is a medical research study involving no intervention and is therefore categorized as an observational study.

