## 5.4 Survey

### (1) Survey items

The following survey and examination will be implemented to evaluate the efficacy and safety of the protocol treatment for subjects in this study.

- ① Medical history
- ② Physical findings
- ③ Diagnostic imaging for evaluation of breast cancer focus
- ④ Survey of adverse events
- ⑤ Treatment survey: the name of the selected medicine and the reasons for the selection, compliance, combined medicine, and treatment
- ⑥ Survey of health-related quality of life (HRQoL)
- ⑦ Survey of aftertreatment
- ⑧ Prognosis survey

The following section, 5.4 (2), specifies the guidelines for conducting surveys ①–⑤ within the range of regular clinical practice while paying careful attention to the burden imposed on patients in this study. In addition, survey of HRQoL will be implemented with attention to the burden imposed on the study subjects. Usually, the time for each survey is limited to 15 minutes and the number of times the survey is carried out is limited to the requisite minimum (3 times in total including at the time of registration, and 1 and 3 months after the initiation of protocol treatment). Surveys at 6 months after the initiation of protocol treatment and later will not be implemented except for the surveys of aftertreatment and prognosis.

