- D) Presence or absence and reasons for implementation of concomitantly used therapies (surgical therapy for breast cancer focus, radiotherapy for breast cancer focus, molecularly-targeted drugs other than mTOR inhibitors, chemotherapy, immunotherapy, other drugs recognized to have antitumor activity against breast cancer) for the past 3 months

(7) Survey plan at 6 months or later after the initiation of protocol treatment or after discontinuation of the protocol treatment

① Timing of survey

- A) Every year from 6 months after the initiation of the protocol treatment when the protocol treatment is ongoing at the time of 6 months after the initiation of the protocol treatment
- B) Every year from the day of discontinuation of the protocol treatment when the protocol treatment is discontinued at the time of 6 months after the initiation of the protocol treatment

② Contents of survey

- A) Continuation state of protocol treatment: Presence or absence of continuation of the protocol treatment. If it is discontinued, the date and reasons for the discontinuation {only for subjects corresponding to the criteria specified in 5.4 (7) ①-A)}.
- B) Survey of progression: Presence or absence of progression defined in 3.9 (2). When progression was observed, the date when the progression occurred was determined (not required for a subject whose progression is already reported.)

- C) Survey of after-treatment: Presence or absence of implementation of chemotherapy. If chemotherapy is implemented, the date and type of chemotherapy.
- D) Survey of prognosis: The final confirmed day of survival. In case of death, the date and cause of death.

(8) Discontinuation of survey

When a case meets one of the following criteria, the survey will be discontinued.

- ① When it is determined that continuation of the rest of the survey is not possible due to changing hospital or other reasons
- ② Withdrawal of consent
- ③ Death
- ④ When it becomes clear that the eligibility criteria are not satisfied
- ⑤ Other reasons, when it is determined that continuation of the study as a subject is not possible

---

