## 5.6 Submission of data

The Case registration card for each subject will be submitted by fax, while other case report forms are submitted to the CSPOR data center via an electronic data capture (EDC) system in this study.

Clinical investigators, clinical research coordinators, and others will submit other case report forms to the CSPOR data center for all patients registered into this study on an ongoing basis until the completion of the study. When the Clinical Research Coordinator or another person completes the case report forms, verification by a clinical investigator is required.

Types of submitted case report forms and the method and timing of distribution/submission are shown below:

| No. | Type                                                 | Method and timing of distribution                                                                   | Method and timing of submission                                                                                               |
|-----|------------------------------------------------------|-----------------------------------------------------------------------------------------------------|-------------------------------------------------------------------------------------------------------------------------------|
| 1   | Case registration card                               | Sent to participating facilities in advance.                                                        | Fax
At the time of registration, within 2 weeks before the scheduled initiation of protocol treatment.                     |
| 2   | Report of initiation of protocol treatment           | EDC                                                                                                 | EDC
Submitted within 2 weeks after the initiation of protocol treatment.                                                   |
| 3   | Progress report (Adverse events, effect measurement) | EDC                                                                                                 | EDC
Submitted within 2 months from each specified date of the 3- and 6-month surveys.                                      |
| 4   | Progress report (After-treatment)                    | EDC                                                                                                 | EDC
Submitted within 2 months from the specified date of the annual survey after the completion of the protocol treatment. |

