### (3) Progress report: During protocol treatment

At 3 and 6 months after the initiation of protocol treatment unless discontinued.

No report at 6 months is required when discontinuation of the protocol treatment is reported in the survey at 3 months.

- ① Body weight, PS
- ② Implementation state of image examinations after the initiation of protocol treatment: 5.3.4 (2) and 5.3.5 (2)
- ③ Focal findings: Descriptions of the site and measurement results for target lesions and non-target lesions.
- ④ Adverse events
- ⑤ Concomitant drugs and treatment, and reasons for implementation
- ⑥ Presence or absence of discontinuation of the protocol treatment. When the treatment is discontinued, the reasons for the discontinuation and date of discontinuation.
- ⑦ Compliance of the protocol treatment
- ⑧ Time point response

(4) Progress report: After-treatment

- ① After-treatment survey: Implementation date and type of chemotherapy

(5) Progress report: Prognosis survey

- ① Presence or absence of progression and date of confirmation  
② Date of last confirmation of survival, date and cause of death (in case of death)

(6) Emergency adverse event report

(See Appendix E)

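### Best overall response is defined up to the start of the next treatment, but response is collected only at months 3 and 6, so the reported RR is a best response by 6 months

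*Protocol*

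**What the plan says.** **Definition.** Protocol 3.8 (6) takes as best overall response "The overall evaluation at the best time point from the initiation of treatment through to the initiation of post-treatment". Section 3.9 (6) rests RR on this: "The response rate is the rate of patients whose best overall response" is CR or PR, counted among patients with measurable lesions. Section 5.10 (3) reports RR by cohort with an exact 90% confidence interval.

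**Collection up to month 6.** Section 3.8 (4) states "Response evaluations will be conducted at about 3 and 6 months", and 5.1 (2) states "A total of 3 imaging evaluations conducted at the time of registration and at 3 and 6 months are specified as investigations in this study". The form carrying lesion measurements and time point response is due "At 3 and 6 months after the initiation of protocol treatment unless discontinued" (5.7 (3)). The table in 5.6 gives its timing as "Submitted within 2 months from each specified date of the 3- and 6-month surveys".

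**Collection after month 6.** Patients still on protocol treatment are surveyed "Every year from 6 months after the initiation of the protocol treatment when the protocol treatment is ongoing" (5.4 (7) ①). Section 5.4 (7) ② lists the content: continuation of treatment, progression and its date, chemotherapy, and survival. It contains no CR, PR or SD and no lesion measurement.

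**The concern.** The definition runs until the next treatment starts, while the response data stop at about month 6. A patient who is SD at months 3 and 6 and first reaches PR at month 9 on the same drug is a responder under 3.8 (6) but SD in the database. Only patients who remain on treatment past month 6 can be affected, and these are the patients doing well.

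At stake is what the published RR means. Following the plan as written, a best response by 6 months would be presented as the best response on treatment, overall and by cohort. Section 4.2 (3) says that the treatment effect expected overall and for each medicine is needed to plan a later comparative trial, so a planner could take the figure at face value.

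**Working it through.** **The plan's own figure.** The protocol gives no expected RR. Its only related calculation is the sample size in 7.3: exact binomial test of CBR, 30% against 50%, one-sided 5%, power 80%. With n = 43 the rule is at least 19 successes, with exact alpha 0.0342 and power 0.8198, so 43 reproduces. Allowing for 10% dropout, 43 / 0.90 = 47.8, or 48, which the protocol sets at 50. This figure concerns CBR and is not in dispute.

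**Definition against data, for a patient still on treatment after month 6.**

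| Item | Window or timing | Source |
|---|---|---|
| Best overall response | Start of treatment to start of next treatment | 3.8 (6) |
| Scheduled response evaluations | About months 3 and 6 | 3.8 (4), 5.1 (2) |
| Lesion measurements, time point response | 3- and 6-month reports only | 5.6, 5.7 (3) |
| Annual survey | Progression, but no response | 5.4 (7) ② |
| Next treatment | Chemotherapy only | 5.3 (6), 5.4 (7) ②, 5.7 (4) |

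No form fills the gap between the first row and the third. The last row adds a second gap: if the next treatment is not chemotherapy, its start, which closes the window, is not recorded.

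**Direction.** Best overall response is a maximum over assessments in the order CR > PR > SD > PD > NE. The maximum over the assessments up to month 6 cannot exceed the maximum over the whole window. Hence RR by 6 months ≤ RR as defined. This needs no assumption about late responders.

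**Size, illustration only.** The inputs are CBR of 30% (threshold) and 50% (expected) from 7.3, used as a rough stand-in for the share still at risk of a late first response. The late-response rate of 5-15% is assumed; the documents give none. Shortfall = CBR × late-response rate:

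- 0.30 × 0.05 = 0.015 and 0.30 × 0.15 = 0.045
- 0.50 × 0.05 = 0.025 and 0.50 × 0.15 = 0.075

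The range is 1.5 to 7.5 percentage points. In a cohort of 50 that is 15 to 25 patients free of progression at month 6 and 0.75 to 3.75 missed responders.

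**Why this is probably an upper range.** CBR (3.9 (1)) requires freedom from progression, not continued treatment. The CBR group also includes patients already in CR or PR by month 6, who cannot become late first responders. RR responders must have measurable lesions, whereas 6.2 (2) enrols patients with or without them. Taking all treated cases as the denominator, as 3.9 (6) does, each restriction shrinks the group that can contribute.

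**The case against.** The strongest defence reads the sections together. Time point response is determined at each imaging evaluation (3.8 (5)), and the protocol specifies only two after baseline. Best response over those two is computable. On this reading, the end of the window in 3.8 (6) merely prevents a response to the next therapy from being credited to protocol treatment. Limited collection is also deliberate in an observational study that keeps its surveys within regular practice, and two fixed assessments are arguably more comparable across cohorts than scans at site-dependent times.

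Part of this stands. A reader might infer that no RR can be computed at all; that goes too far, since a well-defined 6-month RR is available. Stopping at month 6 is also a legitimate choice. But 3.8 (6) does not state that limit. Section 3.9 (1) shows how the protocol writes one when it intends one: the CBR definition names the imaging at 3 and 6 months. Physicians may go on scanning, but no form carries those results to the data center. An analysis plan could narrow the definition; it could not recover data never collected.

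One sentence in 5.4 (1) should carry little weight: "Surveys at 6 months after the initiation of protocol treatment and later will not be implemented except for the surveys of aftertreatment and prognosis". Read literally, it would also exclude the 6-month survey that 5.4 (2), 5.4 (6) and 5.7 (3) schedule. The point holds without it, because the annual survey content in 5.4 (7) ② is explicit.

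**Conclusion.** The mismatch is real and its direction is certain: RR as computed equals RR as defined or falls below it. The gap is confined to patients still on protocol treatment after month 6. Its size cannot be derived from the documents; 1.5-7.5 points rests on an assumed late-response rate and on CBR as a generous stand-in for the group at risk.

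A reader might infer three stronger things, none of which the documents support:

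- That about half of all patients remain on treatment unobserved after month 6. The 50% is an expected rate of freedom from progression, not of continued treatment, and the threshold is 30%.
- That late responses would make up a large part of a low RR. The protocol states no expected RR against which to judge this.
- That the main result is compromised. CBR is fixed at 6 months, so neither it nor the 43 per cohort is touched. RR is a secondary outcome with no threshold, and 7.3 says that the study does not aim to compare cohorts.

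What remains is a secondary outcome whose label promises more than its data can give. It is worth correcting because the correction is cheap.

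**What to change.** Make the definition and the data agree, in one of two ways.

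- **Change the definition.** Restate 3.8 (6) and 3.9 (6) as the best time point response at the 3- and 6-month assessments, and report RR, overall and by cohort, as a 6-month RR. The cost is wording only; RR then makes no claim about later responses.
- **Change the data.** For patients still on protocol treatment, add to the annual Progress report the best response since the last report with its date, plus the start date of any next anticancer treatment, not only chemotherapy. The cost is a few items taken from existing charts, with no extra imaging. The price is uneven ascertainment, because scan timing after month 6 will vary by site.

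The first is the simpler choice and fits the limited collection that the protocol intends.

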### 3.9 Definition of outcome measures in this study

#### (1) Clinical benefit rate (CBR)

The clinical benefit rate is defined as the rate of patients who are not determined to have experienced disease "progression" for 6 months from the initiation of treatment.

"Patients who are not determined as 'progression' for 6 months" means patients whose time point response {3.8 (5) Determination criteria of time point response} based on diagnostic imaging implemented at 3 and 6 months from the initiation of treatment is CR, PR, or SD at any time point, and for whom no clinical progression was observed for 6 months from the initiation of treatment {3.8 (7) Clinical progression}.

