## (5) Time point response

The time point response will be determined at each image evaluation time point in accordance with the criteria specified in the table below based on a combination of the response of target lesions, response of non-target lesion, and incidence of new lesions.

When there are no non-target lesions at baseline, the overall response will be determined based on the response of the target lesion and incidence of new lesions, and when there are no target lesions at baseline, the overall response will be determined based on the response of non-target lesions and incidence of new lesions in accordance with the criteria specified in the table below.

Determination criteria for time point response (when target lesions are present).

| Response of target lesion | Response of non-target lesion | Incidence of new lesion | Overall response |
|---------------------------|-------------------------------|-------------------------|------------------|
| CR                        | CR                            | No                      | CR               |
| CR                        | Non-CR/Non-PD                 | No                      | PR               |
| CR                        | Not evaluated                 | No                      | PR               |
| PR                        | Non-PD or not fully evaluated | No                      | PR               |
| SD                        | Non-PD or not fully evaluated | No                      | SD               |
| Not fully evaluated       | Non-PD                        | No                      | NE               |
| PD                        | Any                           | Yes or No               | PD               |
| Any                       | PD                            | Yes or No               | PD               |
| Any                       | Any                           | Yes                     | PD               |

Determination criteria of time point response (when target lesions are absent).

| Response of non-target lesions | Incidence of new lesions | Overall response |
|--------------------------------|--------------------------|------------------|
| CR                             | No                       | CR               |
| Non-CR/Non-PD                  | No                       | Non-CR/non-PD    |
| Not fully evaluated            | No                       | NE               |

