## 5.10 Method of analysis and assay

(1) Definition of population to be analyzed

The analysis set is defined as below:

Total eligible cases: "Total eligible cases" is defined as a group of patients that overlapped and error registrations are removed from patients who registered in accordance with "5.2 Registration of cases".

Total treated cases: "Total treated cases" is defined as a subgroup of patients among the total eligible cases who received scheduled treatment at least once daily.

(2) Outcome measures

Outcome measures in this study are defined as below:

① Primary outcome measures

- Clinical benefit rate (CBR)

② Secondary outcome measures

- Progression free survival (PFS)
- Overall survival (OS)
- Time to treatment failure (TTF)
- Time to chemotherapy (TTC)
- Response rate (RR)
- Health-related quality of life
- Adverse events (toxicity)

(3) Analysis plan

① Primary analyses

Whether CBR, the primary outcome measures, exceeds 30% will be examined using accurate tests based on binomial distribution and the corresponding 90% confidence interval by cohorts with the entire secondary endocrine therapy. Meanwhile, the analysis set includes all treated cases, and a significance level of 5% is set for 1-sided tests.

② Other analyses

Analysis of the interaction effect of CBR is conducted for responsiveness to the primary endocrine therapy, expression intensity of ER, and presence or absence of PgR expression for all registered cases to examine the significance of effect predictors of the secondary endocrine therapy. The following classification will be used for each factor:

A) Responsiveness to the primary endocrine therapy

- Very low sensitivity group: Recurrence at less than 2 years after the initiation of postoperative endocrine therapy, or progression at less than 3 months after the primary therapy for metastatic breast cancer [corresponding to the ‘very low’ group of Figure 1 in 4.2 (2)].
- Low sensitivity group: Recurrence at 2–5 years after the initiation of postoperative endocrine therapy, or progression at 3–9 months after the primary therapy for metastatic breast cancer [corresponding to the ‘low’ group of Figure 1 in 4.2 (2)].

B) ER expression intensity

- ER low group: ER slightly positive (J-score classification is 1–9%)

- ER high group: ER positive (J-score classification is 10% or higher)

C) Presence or absence of PgR expression

- PgR negative group: PgR negative (J-score classification is negative)

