### 6.2 Inclusion criteria

Cases that satisfy all of the following conditions are included in this study as subjects.

- (1) A patient with estrogen receptor (ER) positiveNote 2 postmenopausalNote 3 breast cancer who is histologically diagnosed as breast cancerNote 1.

Note 1: No distinction is made according to the tissue subtype of cancer.

Note 2: Determination of ER is based on the determination of the primary focus of the breast in accordance with the definition of ER positive that is detailed in section 3.6. In this regard, a case in which evaluation of the primary focus is difficult and which is determined as ER positive based on evaluation of a metastatic lesion can be registered. Furthermore, when the results of evaluation differ between the primary focus and metastatic lesion, the result of the primary focus will be considered for the evaluation of ER expression.

Note 3: At least 1 of the following conditions regarding menopause should be satisfied.

- ① Aged 60 years or older
- ② Younger than 60 years and absence of menstruation for the past 1 year or longer (without hysterectomy)
- ③ Had bilateral oophorectomy

When the presence or absence of menopause of the subject is unclear, FSH and plasma estradiol levels will be measured to confirm whether these are at the after menopausal level as defined by the criteria of each facility.

- (2) Diagnosis of breast cancer corresponds to either of the following. No distinction is made according to the presence or absence of measurable lesions.

- ① Stage IV breast cancer associated with distant metastasis that cannot be a candidate for surgery at the first visit.  
(See 3.3 Classification of clinical stages)
  - ② Breast cancer associated with progression or recurrence caused by distant metastasis after initial treatment (after surgery and treatment before or after the surgery) for breast cancer aiming at curing. However, local recurrence for which radical excision is applicable (this represents the chest wall surrounded by the lower edge of the clavicle as the upper limit of surgical site, the costal arch as the lower limit, the midline of the sternum as interior limit, and the anterior edge of the latissimus dorsi muscle as the outer limit) is excluded.
- (3) Endocrine therapy for metastatic breast cancer is planned.
- (4) Performance status (PS) of ECOG is 0 or 1 Note 4.  
(See 3.5 Evaluation of Performance Status (PS))

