### 7.3 Sample size determination

This study is an observational study, in which therapy is selected based on the preferences of medical staff and patients. The study does not aim to compare different cohorts. To test the major study hypothesis, the threshold clinical benefit rate is set as 30%, and the expected clinical benefit rate is set as 50% in each cohort. Assuming the use of an accurate binomial test, it is estimated that the required number of cases is 43 under a condition of  $\alpha=0.05$  (one-tailed) and  $\beta=0.2$ . Assuming a dropout rate of about 10%, the target sample size estimated to be required for each cohort was set at 50. This study is an observational study, and cases will not always be evenly distributed to each cohort. However, it is needed to set the sample size corresponding to the 4 groups at a maximum [(4) Selection of drugs]. Therefore, a target case quantity of at least 200 was set. Meanwhile, registration will continue until all 4 groups achieve the target number of 50 cases per group within the time frame set for registration, even after a total registration number of 200 cases is achieved.

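### The clinical benefit rate definition in 3.9(1) contradicts itself for patients without target lesions: stable disease counts under its first sentence and fails under its second

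*Protocol*

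**What the plan says.** **Who is enrolled.** On measurable disease, Protocol 6.2(2) states: "No distinction is made according to the presence or absence of measurable lesions". Under 3.8(1), bone lesions without a measurable soft tissue component, effusions, previously irradiated lesions and lymphangitis are all non-measurable. Section 3.8(2) draws target lesions only from measurable ones, so a patient with only such disease has no target lesion.

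**How they are rated.** Section 3.8(5) says that "when there are no target lesions at baseline, the overall response will be determined based on the response of non-target lesions", together with new lesions. The table for this situation offers CR, Non-CR/non-PD, NE and PD. It contains neither PR nor SD.

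**How benefit is scored.** Section 3.9(1) opens by defining CBR as the proportion not judged to have progressed over 6 months. Its second paragraph explains what that means: the time point response under 3.8(5), from imaging at 3 and 6 months, "is CR, PR, or SD at any time point", with no clinical progression over the 6 months. Non-CR/non-PD is not in the list.

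**Who is analysed.** Section 5.10(3) tests CBR in all treated cases, for each cohort and for secondary endocrine therapy as a whole; "a significance level of 5% is set for 1-sided tests".

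**What was planned.** In 7.3, "the threshold clinical benefit rate is set as 30%, and the expected clinical benefit rate is set as 50% in each cohort".

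**The concern.** The two sentences of 3.9(1) give opposite scores to the same patient. Someone with bone-only disease that is unchanged at 3 and 6 months has not progressed, so she benefits under the first sentence. Her time point response is Non-CR/non-PD at both visits, so under the second sentence she does not benefit unless she reaches CR. Nothing in the protocol equates Non-CR/non-PD with SD.

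This is the primary endpoint, and it decides whether each cohort passes the 30% test. If the second sentence is programmed as written, successes are recorded as failures and none move the other way, so the error can only pull CBR down. Treatment is chosen by physician and patient (5.3(1)), so the share without target lesions may differ between cohorts, and each cohort's test would then be affected by a different amount.

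**Working it through.** **Inputs from the protocol.** Threshold 30% and expected CBR 50% in each cohort; one-sided alpha 0.05; beta 0.2; exact binomial test; 43 patients per cohort, raised to 50 for about 10% dropout; at least 200 in total (7.3 and 5.10(3)).

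**Step 1: reproduce the plan's figure.** Section 7.3 reads: "Assuming the use of an accurate binomial test", "it is estimated that the required number of cases is 43 under a condition of" one-tailed alpha 0.05 and beta 0.2. The rejection rule takes the smallest count r with P(X ≥ r | n, 0.30) ≤ 0.05, and power is P(X ≥ r | n, 0.50).
- n = 43: r = 19, actual alpha 0.034, power 0.820.
- Power first reaches 80% at n = 39 (0.832), but is below it again at n = 40 (0.785) and n = 42 (0.780). From n = 43 it stays at or above 80% (checked to n = 60). The figure of 43 is therefore sound under that rule.
- Dropout: 43 / 0.9 = 47.8, so 48, rounded up to 50. At n = 50, r = 21, actual alpha 0.048, power 0.899.
- Overall test, taking 4 × 50 = 200 analysable patients: r = 72, actual alpha 0.040, power about 1.00.

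**Step 2: effect of the literal rule on CBR.** Let q be the share without target lesions, b the true benefit rate (taken as equal in both groups) and c the rate of benefit through CR among those without target lesions. Then

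scored CBR = b(1 − q) + c·q, and the loss is q(b − c).

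The protocol gives neither q nor c. With b = 0.50 and c = 0 as assumptions:
- q = 10%: 0.50 × 0.90 = 45%
- q = 20%: 0.50 × 0.80 = 40%
- q = 30%: 0.50 × 0.70 = 35%

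Scored CBR equals the 30% threshold when q = 1 − 0.30/0.50 = 40%.

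As an illustration, take 50 patients and q = 20%. Ten have no target lesion, and 5 of them truly benefit but are scored as failures. Expected successes fall from 25 to 20, and the test needs 21.

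**Step 3: power with the same critical counts.**

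| Share q | Scored CBR | n = 43 (r = 19) | n = 50 (r = 21) | n = 200 (r = 72) |
|---|---|---|---|---|
| 0% | 50% | 0.820 | 0.899 | 1.000 |
| 10% | 45% | 0.601 | 0.714 | 0.996 |
| 20% | 40% | 0.340 | 0.439 | 0.891 |
| 30% | 35% | 0.136 | 0.186 | 0.409 |

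**Step 4: sensitivity to CR.** With c = 5%, scored CBR is 45.5%, 41.0% and 36.5% at the three shares. Power is 0.626, 0.391 and 0.186 at n = 43; 0.738, 0.497 and 0.252 at n = 50; and 0.997, 0.935 and 0.585 at n = 200.

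**Step 5: after the correction.** If Non-CR/non-PD qualifies, scored CBR returns to 50% and power to 0.820 at n = 43 and 0.899 at n = 50.

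**The case against.** The best defence is that the first sentence of 3.9(1) governs. The second only explains it, and a patient rated Non-CR/non-PD has by that label not progressed. SD in 3.8(4) is also close in meaning, being neither PR-level shrinkage nor PD-level growth. On that reading nobody is lost. A statistical analysis plan, which is not at hand, may say so explicitly.

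Part of this stands. The protocol does not establish that these patients will be scored as failures; it supports both scores. But the second sentence is the one that states the scoring rule, and the SD definition belongs to the target-lesion table. The intended answer is fairly clear, yet the written rule does not deliver it. This is not a detail left for later: the protocol itself fixes the primary endpoint, and does so in two incompatible ways.

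Three stronger readings are tempting and not supported.
- A reader might infer that CBR falls by the whole share of patients without target lesions. It does not: patients who progress, and those who benefit through CR, are scored the same either way. At 50% benefit and no CR, the loss is half the share.
- A reader might take the power figures as a demonstrated loss. They hold only under the literal reading and under assumed values of q, b and c. The overall test at 200 patients keeps about 89% power or more at shares up to 20%.
- A reader might count the best overall response rule in 3.8(6) as a second endpoint error, since "The best overall response will be considered in the order of CR > PR > SD > PD > NE" also omits the category. But CBR uses time point response, and response rate counts only CR or PR, so neither changes.

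**Conclusion.** The point holds as an internal contradiction in the primary endpoint definition. For patients without target lesions, who are eligible and are analysed, the two sentences of 3.9(1) give opposite scores to stable disease short of CR.

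Under the literal rule the loss in CBR is q(b − c). At assumed shares of 10 to 30%, with equal 50% benefit and negligible CR, that is 5 to 15 percentage points. Even the 10% case takes a cohort of 43 from 0.82 to 0.60 power and a cohort of 50 from 0.90 to 0.71. The overall test is much less exposed at 10 to 20%, but falls to 0.41 at 30%. Allowing 5% CR in this group softens the figures without changing the picture.

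The sample size of 43 is correct from its own inputs and is not at fault. The effect is in one direction only: it can make an effective cohort miss the 30% criterion, but cannot make an ineffective one pass.

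**What to change.** In 3.9(1), change the qualifying time point responses to: CR, PR, SD, or Non-CR/non-PD in patients without target lesions. Leave the condition on clinical progression as it is. The second sentence then agrees with the first, and the assumptions behind 7.3 apply to everyone in the denominator.

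The cost is one line. Time point response is already collected in the 3- and 6-month progress reports (5.7(3)), so no new data, visits or patients are needed. Because the wording concerns the primary outcome, the change should go through the protocol's own procedure in 27.4, and any analysis plan should carry the same list.

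Placing Non-CR/non-PD at the SD level in the 3.8(6) ordering would be tidy but is optional, as it alters neither CBR nor response rate.
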